#### Process evaluation

To assess the delivery and feasibility of the PLACES intervention, we will conduct a process evaluation using the model of Linnan and Steckler [37] (see Table 3). This model allows us to identify strengths and weaknesses of the intervention process that can be used to identify necessary improvements to enhance its effectiveness. Several key components of the intervention will be considered, including recruitment, reach, context, dose delivered, dose received, fidelity, and satisfaction.

**Table 3 Tab3:** Overview of process measures according to the model of Linnan and Steckler

Components	Topic	Method of assessment
Recruitment	1. Recruitment route (i.e., hospital, SSA, other) 2. Type of social benefit at baseline (i.e., partially work-disabled, fully work-disabled or on sick leave at the end of their employment contract)	At T0, participants will report the recruitment route and social benefit type. Percentages per recruitment route and type of social benefits will be calculated for all participants and separately for the intervention and control group
Reach	1. The number of people invited, screened and who eventually participated 2. Reasons for non-participation or drop-out 3. Reach of IPS coaches 4. Reach of hospitals	The research logbook reports on: - Invitation, screening and non-participation numbers, with a distinction per labor region (participant reach) - Reasons for nonparticipation or drop-out at baseline, during screening, and throughout the 12-month follow-up period (participant reach) - The number of IPS coaches and hospitals contacted, along with reasons and numbers of nonparticipation (reach of IPS coaches and hospitals) Reach of IPS coaches will additionally be determined by the percentage of participating IPS coaches relative to the total IPS coaches in the Netherlands Reach of hospitals will additionally be determined by the percentage of hospitals relative to the total hospitals with an oncology department in the Netherlands
Context	1. Subgroup analyses to identify factors impacting the intervention implementation 2. Changes in the economic or political structures that influence the SSA 3.The influence of the labor market on intervention outcomes	Subgroup analyses are based on sociodemographic and clinical variables reported at T0 Economic or political changes that may influence the SSA will be reported on in the research logbook The influence of the labor market on the primary outcome will be assessed in interviews with the IPS coach
Dose delivered	Intervention content: 1. Meeting details 2. Total hours spend on delivering the intervention 3. Completion of all three phases 4. Completion of the PLACES & Re-turn training 5. Attendance of intervision meetings	In the IPS coach logbook coaches report on: - Phase completion (yes/no) - Number and duration of meetings - Type of meetings (e.g., face-to-face or video call) - Hours spent on delivering the intervention (e.g., meetings with participants, searching for a job, meeting with employers, on the job support) The research logbook will maintain information on the number of coaches that completed the training and attended the intervision sessions
Dose received	1. Job applications sent 2. Jobs started 3. Participant’s satisfaction with intervention the meetings: amount, duration, timing and content 4. The PLACES & Re-turn training	The IPS coach logbook reports on the number of applications sent and the number of jobs started by the participant The follow-up questionnaires (T1-T3) of participants in the intervention group will assess satisfaction with the intervention: - The satisfaction with the number, duration, and timing of the meetings with the IPS coach will be rated on a 5-point scale (Exactly right/not enough) - The content of the meetings will be rated as good/sufficient/bad Selected IPS coaches will talk about their experiences with the PLACES & Re-turn training. They will rate it as good, sufficient, or bad, and they will be asked if anything was missing from the training
Fidelity	1. Fidelity will be measured by assessing conformation to items and guidelines in the protocol, referred to as performance indicators: - IPS coach contacts participant within 3 working days - First intake meeting: within 2 weeks - First intake meeting: face-to-face - First intake meeting: 60-min duration - All aims of the intake phase are fulfilled - Clear agreements about responsibilities of participants and IPS coach in phase 2 - Contact with employer within 30 days after the initial meeting - Support by IPS coach in finding a suitable job - Support by IPS coach in preparing for job interviews - Support by IPS coach in preparing the start of the job - Meeting with employer, participant and IPS coach, if desirable 2. IPS coach perspective on application of IPS principles	The performance indicators will be assessed based on the IPS coach logbook. Additional information and elaboration on experiences will be drawn from interviews with IPS coaches The performance indicators will be scored as yes/not applicable (score 1) or no (score 0). All indicators will be weighted equally and converted into an overall value of performance. The intervention will be scored sufficient with a minimal score of 75% of the total In semi-structured interviews IPS coaches will be asked to what extent they think that they can apply the IPS principles to cancer survivors
Satisfaction	1. Participant’s satisfaction with the intervention 2. IPS coach’s satisfaction with the intervention 3. IPS coach’s perspectives on their role in supporting cancer survivors 4. Barriers and facilitators when providing the intervention	- Participant satisfaction scores of participants in the intervention group will be measured in the questionnaires at 3, 6, and 12 months on a scale from 1 to 10 - IPS coach’s satisfaction scores and their experiences will be assessed in interviews after the 12-month follow-up. They will be asked to rate their satisfaction on a scale from 1 to 10. They will be asked about their experience in their role in supporting cancer survivors and whether they felt confident in this role. They will also evaluate whether IPS is a suitable intervention for cancer survivors and what the barriers and facilitators are

Quantitative data will be collected using a questionnaire for participants, the IPS fidelity scale, an IPS coach logbook, and a research logbook (Table 3). The process evaluation questionnaire for participants includes questions about recruitment methods (T0) and assesses satisfaction with the intervention and the number, duration, and timing of the meetings (T1–T3). Performance indicators (e.g., completion of all three phases; see Table 3), established based on the IPS fidelity scale, will be evaluated using an IPS coach logbook. Each IPS coach will keep a logbook, providing comprehensive reports on various parameters such as meeting frequency and type per phase, as well as employment-related parameters, such as the number of job applications and interviews. Finally, a research logbook will be maintained, offering detailed information on several stakeholders of the study. Regarding participants, the number of people invited, screened, and included, along with the reasons for nonparticipation or drop-out will be reported. Additionally, the number of IPS coaches, hospitals, and SSA locations contacted for collaboration and the reasons and numbers of nonparticipation will be reported. Finally, qualitative data will be collected through semi-structured interviews with 4–6 IPS coaches and 4–6 participants, aiming to capture their experiences with the intervention and identify any barriers or facilitators influencing its implementation.

### Statistical analyses

To analyze nonparticipation data, we will tabulate the reasons for declining participation at baseline or during the follow-up period, aiming to gain a better understanding of the representativeness of the final study sample. Item frequencies and missing data for all items will be examined. Data cleaning will be performed to address inconsistencies as well as any missing values or improbable answers for the open-ended questions. The sociodemographic and clinical characteristics of the intervention and control group at baseline will be assessed and compared. Established scoring algorithms (as described in Table 2) will be used to calculate scores of the included scales. All analyses will be performed blinded. An independent researcher will code the intervention and control group as either 0 or 1 (with the person doing the analyses not knowing the key).

### Effect evaluation

To evaluate the effectiveness of the PLACES intervention compared to CAU at different time points, mixed-effect regression (either linear or logistic regression) with participant as a random intercept will be conducted. Since we stratified for “received social benefit” and the “labor region,” they will be included as covariates in the model. In all models, the main independent variable will be group allocation (i.e., intervention or control group), and both unadjusted and adjusted models will be presented. Additionally, the influence of time (T1, T2, T3) on the intervention’s effect will be examined (group*time interaction effect). The adjusted models will include potential confounders, such as age, gender, time since diagnosis, type of cancer, type of treatment, importance of work, RTW expectation [15, 38], and baseline value of the dependent variable.

In addition, subgroup analyses will be performed for gender (i.e., male, female or other) time since diagnosis (i.e., ≤ 3 years, > 3 years), type of cancer diagnosis (i.e., breast, colon or other), and type of treatment (i.e., locoregional therapy, systemic therapy or multimodal treatment). All analyses will be performed on an intention-to-treat basis. Per-protocol analyses will be carried out comparing participants in the intervention group who completed at least phase 1 of the intervention and had at least one meeting in phase 2 of the intervention, to participants in the control group.

We will use mixed-effects logistic regression to assess the primary outcome, paid employment [yes/no] at T1, T2, and T3. Odds ratios (ORs) with corresponding 95% confidence intervals (CIs) will be calculated to examine the effect of the intervention on the odds of paid employment.

Differences between the intervention and control group in secondary outcomes will be analyzed using linear or generalized linear regression analyses. Effect sizes and their 95% confidence intervals will be reported for all outcomes. To analyze the secondary outcome “time until paid employment,” a Kaplan–Meier survival analysis will be performed, and differences between intervention and control group will be tested with the log-rank test. In addition, the Cox proportional hazard model, or accelerated failure time analysis if applicable, will be applied to estimate hazard ratios and the corresponding 95% CIs, and the median time until paid employment for the intervention and control group will be determined if possible. All statistical analyses will be conducted using the IBM SPSS Statistics 28.0 [39] or R statistical software version 4.1.3 [40], and the statistical significance will be determined at a two-tailed significance level of 0.05.

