## Methods

A two-armed RCT will be conducted, in which participants will be randomly allocated to (1) the PLACES intervention group or (2) the CAU control group. Participant recruitment, intervention delivery, and measurement timing are shown in Fig. 1. Participants will receive questionnaires at baseline (T0) and after 3 (T1), 6 (T2), and 12 months (T3) follow-up. The participant flowchart is shown in Fig. 2. The “Standard Protocol Items: Recommendations for Interventional Trials” (SPIRIT) 2013 statement was used to structure the design of this study [26] (Appendix S1). In addition to the trial registration (NCT06028048), all items of the World Health Organization Trial Registration Data Set are outlined in Appendix S2.

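### For the continuous secondary outcomes, a random intercept with independent residuals assumes equal correlation over gaps of 3, 6 and 9 months; if correlation decays, intervals for change in the group effect are miscalibrated

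*Protocol article*

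**What the plan says.** The opening paragraph of Effect evaluation in the protocol article sets the general model: "mixed-effect regression (either linear or logistic regression) with participant as a random intercept will be conducted". It adds that "the influence of time (T1, T2, T3) on the intervention’s effect will be examined (group*time interaction effect", and lists among the adjustment variables the "and baseline value of the dependent variable". The responses are therefore the three follow-up waves. The Methods section gives their timing: "Participants will receive questionnaires at baseline (T0) and after 3 (T1), 6 (T2), and 12 months (T3) follow-up". The gaps are 3 months (T1 to T2), 6 months (T2 to T3) and 9 months (T1 to T3).

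The last paragraph of the analysis text for Effect evaluation says: "Differences between the intervention and control group in secondary outcomes will be analyzed using linear or generalized linear regression analyses". It does not repeat the random intercept. Tests are two-sided: "the statistical significance will be determined at a two-tailed significance level of 0.05". No random slope, residual covariance, within-person correlation or standard deviation is given for any continuous outcome.

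**The concern.** A linear random-intercept model with independent, equal-variance residuals has one variance and one correlation for all pairs of waves. With unequal spacing, a person's scores 3 months apart will plausibly agree more closely than scores 9 months apart. The model then applies an average correlation, which is too low for T1 to T2 and too high for T1 to T3.

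The group-by-time terms are built from these within-person differences. The question they answer is whether the benefit of a 12-month programme emerges, holds or fades. If the T1-to-T3 interval is too narrow, chance variation is more easily read as growth or fading. If the T1-to-T2 interval is too wide, a real change between those waves is harder to see.

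**Working it through.** **Inputs.** Waves at 3, 6 and 12 months and the random-intercept model come from the article. There are 74 per arm, half of the 148 evaluable participants in the sample size section. That figure was set for the binary primary outcome, and the plan has no figure of its own on the present point to reproduce. The correlations are assumptions, shown as a range.

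**Formula.** Take complete data, *n* per arm, equal variance σ², and correlation ρ for a given pair of waves. The true variance of the change in group effect between those waves is 4σ²(1 − ρ)/*n*. The random-intercept fit pools the within-person variance, so every pair receives 4σ²(1 − ρ̄)/*n*, where ρ̄ is the mean of the three correlations. Hence

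model SE / true SE = √[(1 − ρ̄)/(1 − ρ)],

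and a nominal 5% test rejects under the null with probability 2[1 − Φ(1.96 × ratio)].

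**Example, 0.8 per 3 months.** The correlations are 0.8, 0.64 and 0.512, so ρ̄ = (0.8 + 0.64 + 0.512)/3 = 0.651.
- T1 to T2: √(0.349/0.200) = 1.32, rejection 1.0%.
- T2 to T3: √(0.349/0.360) = 0.985, rejection 5.4%.
- T1 to T3: √(0.349/0.488) = 0.85, rejection 9.7%.

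**Range.**

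| Assumed correlation at 3 / 6 / 9 months | ρ̄ | T1–T2: SE ratio, rejection | T1–T3: SE ratio, rejection |
|---|---|---|---|
| equal | – | 1.00, 5.0% | 1.00, 5.0% |
| 0.65 / 0.60 / 0.55 | 0.600 | 1.07, 3.6% | 0.94, 6.5% |
| 0.70 / 0.60 / 0.50 | 0.600 | 1.15, 2.4% | 0.89, 8.0% |
| 0.70 / 0.49 / 0.343 | 0.511 | 1.28, 1.2% | 0.86, 9.1% |
| 0.80 / 0.64 / 0.512 | 0.651 | 1.32, 1.0% | 0.85, 9.7% |
| 0.90 / 0.81 / 0.729 | 0.813 | 1.37, 0.7% | 0.83, about 10.3% |

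The T2-to-T3 ratio stays within about 3% of 1 throughout.

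**Simulation** (74 per arm, complete data) agrees. At 0.8 per 3 months the random intercept rejects 1.0% for T1 to T2 and 9.5% for T1 to T3. With an unstructured covariance every contrast is at about 5%.

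**What is not affected.** The variance of the group difference at T1 is 2σ²/*n*, which contains no correlation. The variance of the averaged effect is (2σ²/*n*)(1 + 2ρ̄)/3, which depends only on ρ̄, and the model gets ρ̄ right. In simulation the averaged effect keeps its size (4.8 to 5.1%), and the 2-df interaction test rejects in 5 to 6% of null trials.

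**Power of the 2-df test at 0.8 per 3 months**, by group effect in SD at T1, T2 and T3:

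| Effect pattern | Random intercept | Unstructured |
|---|---|---|
| 0, 0.3, 0.3 | 60% | 73% |
| 0, 0, 0.3 | 57% | 47% |
| 0, 0.15, 0.3 | 45% | 38% |

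Under the mild decay of 0.65 / 0.60 / 0.55, the first pattern gives 53% against 54%.

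**The case against.** Four counter-arguments deserve an answer.

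- **The residual covariance is left open.** The article names a random intercept but says nothing of the residuals. Correlated residuals could be added, and an article may leave that to a fuller plan. This stands in part: the result holds only for the usual independent residuals. But the article does choose a dependence structure, and independent residuals are what that wording ordinarily means.
- **The model for secondary outcomes is ambiguous.** The later sentence on secondary outcomes does not mention the random intercept. The opening paragraph, however, offers a linear version and adjusts for the baseline of the dependent variable. The primary outcome is binary and uses the logistic version, so the linear one can only serve continuous secondary outcomes. The reading is sound, but it is an inference.
- **The size rests on assumed correlations.** This stands. With equal correlations there is no error, and with mild decay the SEs are off by only about 6 to 7%.
- **Little depends on it.** The interaction is an additional analysis, no pairwise contrast between waves is named, and the overall test is nearly correct. This stands too, and it keeps the point minor. A reported interaction would still normally be described through its separate terms.

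A reader might also infer that power to detect an early effect is lost. The documents do not support that. For a 0.3 SD difference at T1, simulated power was 44.6% with the random intercept and 44.2% with an unstructured covariance. The power of the 2-df test can move either way with the effect pattern, as the table shows. Only the T1-to-T2 contrast, taken by itself, is conservative.

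**Conclusion.** The point holds in a limited form. For SF-12, work ability and return-to-work self-efficacy, the model as stated gives intervals for change in the group effect that are miscalibrated if correlation decays with the gap. The T1-to-T3 test then runs at about 6.5 to 10% instead of 5%, and the T1-to-T2 test at about 3.5 to 1%.

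This assumes independent residuals, complete data, equal variances and the correlations tabulated above, none of which the article supplies. It would go too far to say that the intervals are wrong outright, that early effects will be missed, or that the averaged treatment effect is biased. Working hours are recorded only for people in work, and quality of working life presupposes a job. Those waves will be incomplete, and the complete-data figures are only approximate for them.

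**What to change.** For SF-12, work ability and return-to-work self-efficacy, specify a repeated-measures linear mixed model over T1 to T3. Use categorical time, an unstructured residual covariance in place of the random intercept, and the same fixed effects and baseline covariate. State that this model is also what the linear regression for secondary outcomes refers to.

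An unstructured covariance for three waves has six parameters against two for the random intercept. The four extra are a small price with about 148 evaluable participants. T1-to-T3 intervals would widen by about 6% (1/0.94) under mild decay and up to about 20% (1/0.83) in the steepest case shown, which is the correction intended. If correlation is in fact constant, almost nothing is lost. Sample size, data collection and the primary analysis do not change, and both software packages named in the article can fit the model.

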### Sample size calculation

In a previous study of unemployed patients with spinal cord injury, participants who received IPS were significantly more likely to return to paid employment than those in the CAU group (30.8%; 95% CI 21.8–41.6 versus 10.5%; 95% CI 5.2–19.7, respectively) [25]. Based on these data, a power of 80% and an alpha of 0.05, a total of 148 cancer survivors are required to detect the same difference of 20% between the two groups (nQuery Advisor 7.0). Accounting for a 10% loss to follow-up, we aim to include 164 cancer survivors.

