**Participant characteristics**			
Age^a^	1	Participant’s age in years	Continuous
Gender^a,b^	1	Participant’s gender, with response options: male, female, or other	Categorical
Marital status	1	Marital status of participants categorized as: not married, married without children, married with children, living together with partner, living together with partner and children, living together with others, single with children, divorced, widow/widower, or other	Categorical
Children living at home	2	Living arrangement of participants (alone or together) and the number of children living at home	Continuous
Level of education^a^	1	The highest level of education completed by participants with eight answer options according to the Dutch education system, grouped into low, middle, and high, based on the International Standard Classification of Education (ISCED-97)	Categorical
Income^a^	1	Annual income of participants, with response options: < €30,000, €30,000–€60,000, €60,000–€100,000, and > €100,000	Categorical
Financial necessity to work	1	Whether it is a financial necessity for participants to work [yes/no]	Dichotomous
Time since diagnosis^a,b^	1	Time since cancer diagnosis at time of inclusion, calculated from the day (or month, if day is unknown) of diagnosis	Continuous
Type of cancer diagnosis^a,b^	1	The type of cancer diagnosed with answer options: breast cancer, skin cancer, colon cancer, lung cancer, prostate cancer, and other	Categorical
Type of cancer treatment^a,b^	5	Types of cancer treatment(s) received (e.g., surgery, radiation, chemotherapy, hormonal therapy, or a combination), duration of treatment, current treatment, and future treatment (e.g., hormone therapy)	Categorical
Importance of work^a^	1	Importance of work measured on a visual scale from 0 (not important at all) to 10 (very important)	Continuous
RTW expectation^a^	1	Participant’s estimation of the chances they will be at work in 6 months on a scale from 1 (no chance) to 10 (very high chance)	Continuous

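### The adjusted logistic model for paid employment puts about 14–24 or more parameters on roughly 31 participants with the event, which inflates the odds ratio; its baseline term is not usable for this outcome

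*Protocol article*

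**What the plan says.** All points are in the Protocol article.

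- **Model (Effect evaluation).** Paid employment at T1, T2 and T3 is analysed by mixed-effects logistic regression with a random intercept per participant. Group is the main term, benefit type and labour region enter as covariates, and time and its interaction with group are examined. The section adds that "both unadjusted and adjusted models will be presented".
- **Adjustment list (same section).** "The adjusted models will include potential confounders, such as age, gender, time since diagnosis, type of cancer, type of treatment", then work importance, return-to-work expectation and "baseline value of the dependent variable". The sentence covers every outcome and makes no exception for the primary one.
- **Coding (Table 2).** The answer options for cancer type are "breast cancer, skin cancer, colon cancer, lung cancer, prostate cancer, and other". Gender has three options and social benefit three categories. Education and income are also flagged as potential confounders. Effect evaluation gives three-group versions of cancer type and treatment, but for the subgroup analyses only.
- **Planning (Sample size calculation).** The rates are "30.8%; 95% CI 21.8–41.6 versus 10.5%; 95% CI 5.2–19.7, respectively". The evaluable number rests on "a power of 80% and an alpha of 0.05, a total of 148 cancer survivors are required", for a difference of 20 percentage points, and the target is 164 after 10% loss. Testing is at a "two-tailed significance level of 0.05".
- **Primary item (Primary outcome measure).** Paid work since the previous questionnaire is asked at T1–T3.

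**The concern.** Maximum-likelihood logistic regression with few events per parameter biases odds ratios away from 1. When a category contains no events, or only events, the fit separates and gives no finite estimate for that category. Here the bias would favour the intervention whenever a benefit exists. The adjusted odds ratio will stand beside a smaller unadjusted one, and the article does not say which carries the conclusion, so a reader could take the larger figure as the better-controlled estimate of a stronger effect.

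The baseline term is a separate and smaller matter. It suits the continuous outcomes, but for paid employment there is little or nothing to put in it.

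**Working it through.** **1. The plan's own figure.** Two-sided 0.05, power 80%, 1:1, n per arm = [1.96·√(2p̄q̄) + 0.842·√(p₁q₁ + p₂q₂)]² / d².
- At 30.8% and 10.5% (d = 0.203, p̄ = 0.2065): (1.122 + 0.466)² / 0.0412 = 61.2, so 62 per arm and 124 in total.
- With continuity correction, n/4·[1 + √(1 + 4/(n·d))]²: 70.7, so 71 per arm and 142 in total.
- The corrected formula gives 144 at 30% and 10%, and 148 at 31% and 11%.

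So 148 is reproduced with a continuity correction and rounded rates. 148/0.9 = 164.4, stated as 164.

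**2. Participants with the event.** 74 × 0.308 + 74 × 0.105 = 22.8 + 7.8 = 30.6. With all 164 followed: 82 × 0.413 = 33.9.

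**3. Parameters (without the intercept).**
- Group 1, benefit type 2, age 1, gender 1 (two levels), years since diagnosis 1, treatment 2 (three groups), work importance 1, return-to-work expectation 1: 10.
- Cancer type: 2 (three groups) or 5 (Table 2).
- Region: 2, 4 or 9 for 3, 5 or 10 regions. The number is an assumption.

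This gives 10 + 2 + 2 = 14 (collapsed cancer, 3 regions), 10 + 5 + 4 = 19 (six-level cancer, 5 regions) and 10 + 5 + 9 = 24 (six-level cancer, 10 regions). Not counted: time and its interaction (4), the baseline term (1), a third gender level (1), education and income (5).

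**4. Events per parameter.** 30.6/14 = 2.2; 30.6/19 = 1.6; 30.6/24 = 1.3.

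**5. Simulation, one yes/no outcome per person, N = 148, true conditional odds ratio 4.1.** Covariate distributions are assumed.
- Three-level cancer coding: median adjusted OR 4.9–5.7.
- Six-level cancer coding: 5.2–6.2.
- Relative to the truth: 4.9/4.1 = 1.20 and 6.2/4.1 = 1.51, so 20–51% too high on the odds-ratio scale.
- Firth-penalised fit: 3.9–4.0.
- Separation or non-convergence: 2–4% of runs with three-level cancer and 3–5 regions; 37–61% with six-level cancer or 10 regions.
- Shorter model (group, benefit type, region as fixed effects, return-to-work expectation): 4.4–4.9, failing in about 40% of runs with 10 regions.

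A second simulation with other assumed distributions (1,500 runs per row, true conditional OR 3.8 or 4.3) agrees:

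| Parameters | N | Bias of log OR | Failed fits | 95% CI coverage |
|---|---|---|---|---|
| 15 | 148 | +17% to +22% | 4–5% | 92–94% |
| 21 | 148 | +25% to +33% | 45–48% | 90–91% |
| 23, with a rare gender category | 148 | +32% to +36% | about 80% | 88–90% |
| 21 | 164 | +28% | 41% | 90% |

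Firth medians at N = 148 were 3.5–4.4.

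**6. Do repeated visits help?** In a small random-intercept simulation (120 runs per scenario), about 55 employed person-visits came from about 31 people. The covariates are person-level, so the information on them is still limited by those 31. Some category had no events in 3% of runs with collapsed coding and 52% with six-level cancer. The median adjusted-to-unadjusted OR ratio was 1.48 with 17 parameters and 1.14 with 21. This is not a clean measure of bias, because the fitted random-intercept SD was large and differed between the two fits.

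**7. Baseline term.** The primary item refers back to the previous questionnaire and is asked only from T1, so no T0 value is described. If current employment at entry were used instead, eligibility (Participants and recruitment) requires people to be unemployed and sick-listed and/or work-disabled. Some partially disabled entrants might hold some work, so the variable is nearly constant rather than strictly constant.

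**The case against.** The strongest reply is that the article does not fix a model. The list is introduced as examples, and coding, number of regions and a convergence fallback commonly belong to an analysis plan that is not shown. That stands for those details, and their absence is not the point here. The stratification factors, seven named covariates and the baseline value are nevertheless stated as going into the adjusted model. Even the collapsed version of that list inflates the odds ratio.

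A reader might infer more than the documents support:

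- *That the model will often fail to fit.* This depends on coding and on an unknown number of regions. With the three-group cancer coding that the plan already has for subgroups, and few regions, failure is rare.
- *That 4.9–6.2 predicts the trial's adjusted result.* Those figures come from a single outcome per person, not from the planned random-intercept model, whose odds ratios are on another scale.
- *That any gap between adjusted and unadjusted estimates is artefact.* Some gap is expected because odds ratios are non-collapsible. The bias figures in the single-outcome simulations are measured against the true conditional odds ratio, so they exclude that part.
- *That the baseline term drives the bias.* It does not. A constant column would drop out, and the term is not in the parameter count.
- *That shortening the list is enough.* It is not. With region as fixed effects, some inflation remains, and ten regions alone cause many failed fits.

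Presenting the unadjusted model is a partial safeguard: the discrepancy would be visible, though its cause would not.

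**Conclusion.** The concern holds for the adjusted analysis of paid employment. About 31 participants with the event follows directly from the plan's rates. The 14–24 parameters follow from the listed covariates, with an assumed 3–10 regions and either cancer coding, and more would enter if time terms, education and income were added. In single-outcome simulations the adjusted odds ratio was inflated by about 20–51%, under collapsed coding too. Frequent separation is conditional on six cancer levels or many regions. The direction carries over to the repeated-measures model, because the events come from the same people, but the exact size does not.

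The baseline term is a small, separate wording error that concerns this outcome only. The unadjusted comparison and the continuous outcomes are not affected. The plan should be changed, but the trial's design is not in question.

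**What to change.** In Effect evaluation:

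1. Name one primary model for paid employment: group, benefit type and region, with region collapsed to a few levels or entered as a random effect. Add at most one or two prognostic covariates chosen in advance; return-to-work expectation is one option.
2. State that the baseline value of the dependent variable is not used for paid employment, and keep it for the outcomes measured at T0.
3. Move the full covariate list, with collapsed categories, to a sensitivity analysis with a penalised (Firth-type) fit, for example on the single ever-employed outcome over 12 months. This avoids having to combine the penalty with the random intercept.

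The cost is analysis wording only, with no change to recruitment or data collection. The drawbacks are fewer covariates in the main model, and a sensitivity analysis on the ever-employed outcome that does not mirror the visit-by-visit model. The handling of region cannot be skipped, since a short model with many fixed region terms still performs poorly.
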